Questionnaires: perceived stress according to Cohen’s Perceived Stress Scale; quality of life according to the WHO Quality of Life-BREF (WHOQOL-BREF); self-rated depressive symptoms according to Beck’s Depressive Inventory (BDI); self-rated depressive symptoms according to the Hamilton Depression Self-rating Scale 6-item (HDRS-6); self-rated manic symptoms according to the Altman Self-rating Scale for Mania (ASRM) (only for patients with a bipolar disorder diagnosis); recovery according to the Recovery Assessment Scale; empowerment according to Rogers’ Empowerment Scale; adherence to medication according to the Medicine Adherence Rating Scale; wellbeing according to the WHO (five) Wellbeing Index; rumination according to the Rumination Response Scale (RRS); worrying according to the Penn State Worry Questionnaire (PSWQ); satisfaction according to the Verona Satisfaction Scale-Affective Disorder (VSS-A). The HDRS-6, the ASRM and the WHO (five) are filled out every month during the study 6-month period

Clinical information: re-admissions and duration of re-admissions (register data); number of affective episodes; number of contacts with clinicians and psychiatric emergency rooms; hospitalizations; medication, etc

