### Assessments

Researchers blinded to the patients’ allocation of intervention group ([name] and one other physician) who are not involved in the treatment of the patients carry out all outcome assessments. The unipolar disorder or bipolar disorder diagnoses according to ICD-10 are confirmed by a SCAN interview before inclusion of the patients. The patients are, regardless of randomization group, enrolled for a 6-month trial period and invited for outcome assessments by researchers blinded to intervention at baseline, after 3 months and after 6 months (Table 1).

At each visit with the researchers, the assessments include the following:

1. Clinician-administrated rating scales: the severity of depressive and manic symptoms (manic symptoms only assessed for patients with a bipolar disorder diagnosis) is measured using the Hamilton Depression Rating Scale 17-item (HDRS-17) [52] and the Young Mania Rating Scale (YMRS) [34], respectively, and psychosocial functioning is measured using the Functioning Assessment Short Test (FAST) [53]

2. Questionnaires: perceived stress according to Cohen’s Perceived Stress Scale [54], quality of life according to the WHO Quality of Life-BREF (WHOQOL-BREF) [55], self-rated depressive symptoms according to Beck’s Depressive Inventory (BDI) [56–58], self-rated depressive symptoms according to the Hamilton Depression Self-rating Scale 6-item (HDRS-6) [59], self-rated manic symptoms according to Altman Self-rating Scale for Mania (ASRM) (only for patients with a bipolar disorder diagnosis) [34], recovery according to the Recovery Assessment Scale [60], empowerment according to Rogers’ Empowerment Scale [61], adherence to medication according to the Medicine Adherence Rating Scale [62], wellbeing according to the WHO (five) Wellbeing Index [63], rumination according to the Ruminative Response Scale (RRS), worrying according to the Penn State Worry Questionnaire (PSWQ) [64], and satisfaction according to the Verona Satisfaction Scale-Affective Disorder (VSS-A) [65]. The patients are asked to fill out HDRS-6, ASRM (only for patients with a bipolar diagnosis) and WHO (five) every month during the 6-month trial period in both groups and in both trials.

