### Statistical power and sample size calculation

The statistical power and sample size was calculated using http://stat.ubc.ca/~rollin/stats/ssize/n2.html.

The primary outcomes are differences in the number and duration of re-admissions to a psychiatric hospital between the intervention group and the control group − analyzed separately according to psychiatric diagnosis (unipolar disorder or bipolar disorder). Power calculations are similar for the two RCTs/patient groups (unipolar disorder or bipolar disorder). Based on prior findings aiming to reduce re-hospitalization due to recurrent depression [66] and bipolar disorder [9], combined with presumptions of positive effects of the immediate early contact with patients during the vulnerable period following discharge from a psychiatric hospital, regardless of diagnosis, we expect a reduction in re-admissions from 30% to 15% in the intervention group using smartphone-based treatment. Thus, anticipating a hazard ratio (HR) of 0.50 in the comparison of the intervention group with the control group on the primary outcome, a two-sided risk of type 1 error, *α* of 0.05, a type 2 error risk, *β*, a statistical power of 80%, the sample size (*N*) is calculated as *N* = 200 (100 patients in each arm of each RCT) per RCT and, thus, a total of 400 patients (200 patients with unipolar disorder and 200 patients with bipolar disorder) is estimated to be required for the RADMIS trial. Cumulated durations of re-hospitalizations comprise similar power calculations and sample sizes. Regarding the secondary outcomes, the clinically relevant difference in depressive or manic symptoms is defined as a minimum of three scores on the HDRS-17 or on the YMRS, respectively, and the standard deviation (SD) is set at 7 with a mean score of 12 versus 15 in the intervention group and the control group, respectively. The statistical power to detect a three-score difference in the areas under the curves between the intervention and the control groups on the HDRS-17 or the YMRS, respectively, is 80% with *α* = 0.05 for a two-sample comparison of means including a total of 200 patients (100 patients in each arm) in each of the two RADMIS RCTs.

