### Statistical methods

Data from all randomized patients are collected until dropout or the end of the trial period. Analysis will be carried out with an intention-to-treat (ITT) approach. The primary outcomes are differences in time to re-admission and duration of re-admissions during the 6-month trial period between the intervention group and the control group. Time to the first re-admission will be estimated using a Kaplan-Meier plot with reasons for censoring being date of death or end of study. The differences in cumulated prevention of re-admission in the intervention group and the control group will tested using a log-rank test. Analysis of secondary and tertiary outcomes will be done employing a linear mixed-effects model with random intercept for each participant and a fixed effect of visit. Differences in outcomes between the intervention group and the control group will be analyzed, firstly in an unadjusted model (except for differences in baseline values of the outcome variable in analyses on continuous variables) and then in models adjusted for the two stratification variables (1) psychiatric center and (2) the number of prior hospitalizations, and also for age and sex as possible prognostic variables. If there are no statistically significant main effects of age and sex, these variables will be excluded from the final analyses. Furthermore, subanalyses will be done employing a linear mixed-effects model with random intercept for each participant and a fixed effect of visit on differences in the HDRS-17 and the YMRS in patients with the presence of depressive and manic symptoms (defined as HDRS-17 > 0 or YMRS >0, respectively) at a given time point during the trial period between the intervention group and the control group. Additionally, in addition to analyses of the secondary outcomes, we will analyze differences in depressive and manic episodes defined as HDRS ≥14 and YMRS ≥14, respectively, during the trial period. Potential interactions between randomization group and visit number on any specific outcome variable in the analyses will be investigated and reported accordingly. The statistical threshold for significance is *p* ≤ 0.05 (two-tailed). Data will be managed by [name] and entered using Epidata®. All analyses will be done using SPSS, version 22.0 (IBM, New York, NY, USA) and STATA version 12 (StataCorp LP, College Station, TX, USA).

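### A random intercept alone makes the group-by-visit tests on the monthly self-rated scales anti-conservative if within-patient correlation falls with time

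*Protocol article*

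**What the plan says.** The Statistical methods section of the protocol article assigns one model to all secondary and tertiary outcomes: a "linear mixed-effects model with random intercept for each participant and a fixed effect of visit". The same model is named again for the subanalyses of HDRS-17 and YMRS in symptomatic patients. No random slope, serial residual correlation or robust standard error is mentioned, and none is ruled out.

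The section then adds: "Potential interactions between randomization group and visit number on any specific outcome variable in the analyses will be investigated and reported accordingly". The significance threshold is two-sided 0.05. The text does not say whether visit is a set of categories or a linear term. Group comparisons are unadjusted at first, "except for differences in baseline values of the outcome variable in analyses on continuous variables".

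The researcher assessments take place "at baseline, after 3 months and after 6 months" (Assessments). The notes to Table 1 (Study procedure) add a denser schedule for three questionnaires: "The HDRS-6, the ASRM and the WHO (five) are filled out every month during the study 6-month period". ASRM is restricted to patients with bipolar disorder. All three scales are tertiary outcomes.

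**The concern.** With a random intercept and independent residuals, scores one month apart are assumed to be as strongly correlated as scores five months apart. Patients enter at discharge after an affective episode, and their mood scores may well be more alike in adjacent months than in distant ones. A group-by-visit test is built from within-patient differences, so its standard error depends directly on that assumption. If correlation really decays, the pooled within-patient variance is too small for slow changes over time.

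At stake is a report that the intervention effect builds up or fades after discharge when it does not. This concerns five analyses: HDRS-6 and WHO-5 in the unipolar trial, and HDRS-6, WHO-5 and ASRM in the bipolar trial.

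**Working it through.** **The plan's own figures.** The article gives no correlation, standard error or error rate for the group-by-visit test. Its only power figure for an outcome under this model is 80% for a 3-point difference in HDRS-17 or YMRS ("the standard deviation (SD) is set at 7 with a mean score of 12 versus 15"), "including a total of 200 patients (100 patients in each arm) in each of the two RADMIS RCTs". The usual formula gives 3 / (7·√(2/100)) = 3.03, and Φ(3.03 − 1.96) = 0.858. The stated 80% is therefore conservative, and it has no bearing on this point.

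**Inputs.** From the article: 100 per arm, two-sided 0.05, random intercept, six monthly follow-ups. Assumed, because the article does not give them: complete data, equal variance at each visit, model-based standard errors, and the true correlation R. R was varied over constant correlation 0.5, serial correlation ρ^lag with ρ from 0.5 to 0.9 per month, and a random intercept plus a decaying part.

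**Formula for a linear trend in visit number.** With variance 1, let c be the centred months (−2.5, −1.5, −0.5, 0.5, 1.5, 2.5), so c′c = 17.5.
- The model uses the within-patient mean square, 1 − r̄, where r̄ is the mean off-diagonal correlation.
- The true variance of the contrast, on the same scale, is c′Rc / c′c.
- The ratio of true to model standard error is √[(c′Rc / 17.5) / (1 − r̄)].
- Actual type I error is 2·[1 − Φ(1.96 / ratio)].

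**Worked case, ρ = 0.7.**
- r̄ = (5·0.7 + 4·0.49 + 3·0.343 + 2·0.2401 + 0.1681) / 15 = 0.476, so the model variance is 0.524.
- c′Rc = 17.5 + 2·(8.75·0.7 + 1·0.49 − 4.75·0.343 − 7.5·0.2401 − 6.25·0.1681) = 21.77, and 21.77 / 17.5 = 1.244.
- Ratio = √(1.244 / 0.524) = 1.54. Type I error = 2·[1 − Φ(1.27)] = 20%.

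When R is a random intercept plus a decaying part, the intercept cancels from both variances, so the ratio is that of the decaying part alone.

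**Rejection rates with no true effect, months 1–6.** Simulated with 10,000 runs per row, or 4,000 where marked *.

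| True correlation | Average group contrast | Group-by-visit, categorical | Group-by-visit, linear | Linear, by formula |
|---|---|---|---|---|
| constant 0.5 | 4.8% | 4.6% | 5.1% | 5.0% |
| 0.5 + 0.5·0.3^lag * | not run | 5.5% | 10.0% | 10.7% |
| 0.5^lag | 4.7% | 6.0% | 15.3% | 15.4% |
| 0.4 + 0.6·0.5^lag | 5.2% | 6.8% | 15.7% | 15.4% |
| 0.7^lag | 4.8% | 7.5% | 20.3% | 20.3% |
| 0.8^lag | 4.9% | 8.4% | 22.7% | 22.7% |
| 0.9^lag | 5.1% | 9.1% | 25.1% | 25.0% |

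Over ρ = 0.5 to 0.9 the true standard error of the trend is 1.38 to 1.70 times the model's. Tests with unstructured covariance, run with 4,000 datasets for ρ = 0.5, 0.7 and 0.8 and for two random-intercept-plus-decay patterns, rejected in 4.5–5.5%.

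**Where the effect stops.**
- Responses at 3 and 6 months only, baseline as covariate: there is a single lag, so no lag pattern can be misspecified. Interaction tests rejected in 4.9–5.2%.
- Baseline, 3 and 6 months all as responses: categorical 4.8–5.3% for ρ = 0.5 to 0.8 and 5.9% at 0.9; linear 5.6–8.0% and 9.8% respectively.
- Group difference at the last monthly visit: 4.6–5.3% in the 10,000-run settings. With equal variances the model gets the total variance right, so visit-specific intervals hold.
- Month 0 added as a seventh response: categorical 6.7–9.8%, linear 17–29%.

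**The case against.** The strongest reply is that nothing is shown to be wrong. The article is a condensed account, and residual covariance, type of standard error and coding of visit are details that an analysis plan commonly settles. The article uses the word visit for the researcher assessments at 0, 3 and 6 months; the monthly questionnaires are simply filled out. If only the 3- and 6-month scores are responses, the problem does not arise. The larger error rates need a linear term, which the article does not state. The interaction analysis is exploratory, and the scales are tertiary and already acknowledged to be unblinded.

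Most of this stands, and it is why the point is conditional and minor. It does not remove the point. The article does not leave the within-patient structure open: it names a random intercept and nothing else, and it promises interaction results on any outcome variable. It also collects three scales monthly, and the reference to visit number allows a linear reading.

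A reader might go further and infer that the standard errors are simply wrong, that visit-specific intervals fail, or that the main treatment comparisons are compromised. The documents do not support any of these. No correlation is given, and with constant correlation the level is nominal. Visit-specific intervals are correct when variances are equal. The average contrast held at about 5% in every setting run. A reader might also count ASRM in both trials, but it belongs to the bipolar trial only.

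**Conclusion.** The concern holds in a limited, conditional form. For HDRS-6 and WHO-5 in both trials and ASRM in the bipolar trial, the stated model does not protect the 5% level of the group-by-visit test if three conditions hold together: monthly scores are the responses, correlation decays with lag, and standard errors are model-based. The excess is modest with visit as categorical (about 6–9%) and large only with visit number as a linear trend (about 10–25%).

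The primary outcomes are outside the point: re-admission data come from the register, and time to first re-admission is tested by log-rank, so this model does not enter. The secondary rating scales are unaffected when baseline is a covariate, as the article's baseline adjustment suggests. Unequal variances over time and dropout were not examined. This is a worthwhile refinement and does not threaten the trial's main conclusions.

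**What to change.** Keep the linear mixed model. For the monthly scales, specify an unstructured residual covariance across visits. Name a fallback in case it does not converge: a random intercept plus autoregressive residuals, or cluster-robust standard errors. State that visit is categorical in the group-by-visit test.

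The change takes about one line in the analysis plan and alters no outcome, visit schedule or sample size. The price is a few more covariance parameters and possibly having to use the fallback. Little is lost if the correlation turns out to be constant.

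### The HDRS-17/YMRS subanalysis selects patients on a post-randomisation value of the outcome itself, so its between-arm estimate can be biased in either direction

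*Protocol article*

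**What the plan says.** All of this is in the protocol article.

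- **General principle (Statistical methods):** "Analysis will be carried out with an intention-to-treat (ITT) approach".
- **Main secondary analysis (same section):** "Analysis of secondary and tertiary outcomes will be done employing a linear mixed-effects model", with no restriction on the score.
- **Further subanalysis (same section):** "subanalyses will be done employing a linear mixed-effects model with random intercept for each participant and a fixed effect of visit on differences in the" two symptom scales, HDRS-17 and YMRS. It is limited to outcomes "in patients with the presence of depressive and manic symptoms (defined as HDRS-17 > 0 or YMRS >0, respectively) at a given time point", and the time window and contrast are "during the trial period between the intervention group and the control group".
- **Planning figures (Statistical power and sample size calculation):** "the clinically relevant difference in depressive or manic symptoms is defined as a minimum of three scores on the HDRS-17 or on the YMRS", and "the standard deviation (SD) is set at 7 with a mean score of 12 versus 15 in the intervention group and the control group". The section states 80% power with 100 patients per arm at α = 0.05.
- **Assessment times (Assessments; Table 1):** HDRS-17 is rated at baseline, 3 months and 6 months in both trials, and YMRS at the same visits in bipolar patients only.

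**The concern.** Two of the three rating visits come after randomisation, and at those visits the score already reflects any treatment effect. A patient who reaches 0, the best possible result, leaves the restricted sample (or that visit does). A comparable patient in the other arm who does not reach 0 stays. The patients left in each arm then differ for reasons tied to treatment, and their difference in means no longer estimates a treatment effect in a group fixed at randomisation.

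At stake is how a supplementary result on two secondary outcomes is read. A smaller, larger or reversed difference could come from who was selected and be taken for an effect on symptom severity.

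**Working it through.** **Step 1. The plan's own power figure.** Inputs: difference 3, SD 7, 100 per arm, two-sided α 0.05.

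- Standard error = 7 × √(2/100) = 0.990.
- Power = Φ(3/0.990 − 1.96) = Φ(1.07) = 85.8%.
- Patients needed for 80% = 2 × (1.96 + 0.8416)² × 7²/3² = 85.5, so 86 per arm.

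The stated 80% is therefore conservative, and the point below does not depend on it. An SD of 7.57 would give 80% at 100 per arm.

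**Step 2. Effect of the restriction at the plan's inputs, one visit.** Treat the score as normal with mean m and SD 7, recorded as 0 when the underlying value is below 0.5. Let a = (0.5 − m)/7.

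- Share above 0: p = 1 − Φ(a).
- Mean among scores above 0: m + 7 × φ(a)/p.
- Mean in all patients: p times that value.

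| Arm | a | Share at 0 | Mean, score > 0 | Mean, all |
|---|---|---|---|---|
| Control, m = 15 | −2.071 | 1.9% | 15.33 | 15.04 |
| Intervention, m = 12 | −1.643 | 5.0% | 12.76 | 12.12 |

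- All patients: 15.04 − 12.12 = 2.92. This is below 3 because of the floor.
- Scores above 0: 15.33 − 12.76 = 2.57.
- Loss: (2.92 − 2.57)/2.92 = 12%. Power in the restricted set is about 79%.

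**Step 3. The two post-randomisation readings of the time-point wording.** Simulation with two follow-up visits, within-patient correlation 0.5 (an assumption; the documents give none).

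| Underlying means, SD 7 | All data | Zero-score visits dropped | Patients with any follow-up score > 0 kept |
|---|---|---|---|
| 15 vs 12 (plan) | 2.92 | 2.57 | 2.82 |
| 4 vs 1 (assumed) | 1.93 | 1.30 | 1.49 |

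In the plan's case the loss is 12% or about 3.5%, depending on the reading. In the second row, 31% of controls and 47% of intervention patients score 0 at a visit. The loss is then about a third or about 23%. That row shows what many zeros would do and has no source in the documents.

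**Step 4. Direction.** A constructed example: controls have 50% at 0, 25% at 3 and 25% at 10.

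| | Mean, all | Mean, score > 0 |
|---|---|---|
| Control | 0.25 × 3 + 0.25 × 10 = 3.25 | (3 + 10)/2 = 6.5 |
| Treatment brings only the 3s to 0 | 0.25 × 10 = 2.50 | 10.0 |
| Treatment brings only the 10s to 0 | 0.25 × 3 = 0.75 | 3.0 |

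- Mild cases cleared: a true benefit of 0.75 appears as harm of 3.5.
- Severe cases cleared: a true benefit of 2.5 appears as 3.5.

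**Step 5. Remission starting from the plan's control distribution (mean 15, SD 7).**

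- If a random 20% of intervention patients go to 0, the benefit is 3.0 in all patients and 0.0 among scores above 0.
- If the mildest 38% go to 0, a benefit of 3.1 becomes apparent harm of 4.0.

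Both patterns are constructed to show the possible range; they are not forecasts.

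**The case against.** The strongest defence is that this is an extra analysis. The main mixed models use HDRS-17 and YMRS without a score restriction under the intention-to-treat statement, and the primary outcome comes from register data. A benefit lost in the subset would still show in the unrestricted result. This stands, and it limits the weight of the point.

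Next, few patients would score 0 at the plan's inputs, so the loss is modest. Only an exact 0 excludes anyone. A patient who improves to between 1 and 13, below the protocol's episode threshold, stays in. This also stands: it would be wrong to say that the rule removes everyone whom the intervention made well.

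A reader might infer that the subanalysis is always biased against an effective treatment. The documents do not support that, because Step 4 shows inflation when severe cases clear. A reader might also infer that zeros will be common on YMRS, or that a reversed sign is likely. The article gives no distribution of scores, and its power section uses SD 7 and a three-point difference for both scales. Nor does it say how the subanalysis will be weighted, so the claim that it would be presented as a randomised comparison is only a prediction.

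Finally, the time-point wording is ambiguous. Selection on the baseline score alone would avoid the problem, but a window described as during the trial period does not say that. The two post-randomisation readings both attenuate the difference at the plan's inputs, by different amounts.

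**Conclusion.** The point holds as a moderate one. The restriction is a stated rule, so it is not a detail left to an analysis plan that is not shown. It conditions on the outcome after randomisation, which costs this one comparison its randomised basis. The direction of the bias is unknown in advance.

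At the plan's inputs the attenuation is about 12% (2.92 to 2.57) if zero-score visits are dropped. It is about 3.5% (2.92 to 2.82) if patients with any follow-up score above 0 are kept. Both figures assume a normal score floored at 0, and the second also assumes a within-patient correlation of 0.5. Erasure or reversal rests on many zeros or selective remission to exactly 0. Both are assumptions, more plausible for YMRS than for HDRS-17. Conclusions on re-admission and from the unrestricted secondary models are not affected.

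**What to change.** Change one sentence in Statistical methods, in one of these ways:

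- **Baseline subset.** Define symptomatic patients by the pre-randomisation score (HDRS-17 > 0 or YMRS > 0 at baseline).
- **Interaction.** Test treatment by baseline score in all randomised patients.
- **If the zeros themselves are the worry.** Keep everyone and use a two-part or ordinal mixed model.

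If the current restricted analysis is kept, say whether zero-score visits or never-symptomatic patients are dropped. State also that the analysis is descriptive and supports no claim of a treatment effect.

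The cost is small, since baseline ratings are already collected. The one trade-off is that a baseline-defined subset asks about patients symptomatic at entry, a slightly different question from how severe symptoms are when present.
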